**Methods:**

A 12-week community-based PR will be implemented in primary healthcare centres where programmes are not available. Healthcare professionals will be trained. 73 patients with CRD and their caregivers (dyads patient-caregivers) will compose the experimental group. The control group will include dyads age- and disease-matched willing to collaborate in data collection but not in PR. Patients/family-centred outcomes will be dyspnoea (modified Medical Research Council Questionnaire), fatigue (Checklist of individual strength and Functional assessment of chronic illness therapy – fatigue), cough and sputum (Leicester cough questionnaire and Cough and sputum assessment questionnaire), impact of the disease (COPD Assessment Test), emotional state (The Hospital Anxiety and Depression Scale), number of exacerbations, healthcare utilisation, health-related quality of life and family adaptability/cohesion (Family Adaptation and Cohesion Scale). Other clinical outcomes will be peripheral (biceps and quadriceps-hand held dynamometer, 1 or 10 repetition-maximum) and respiratory (maximal inspiratory and expiratory pressures) muscle strength, muscle thickness and cross sectional area (biceps brachialis, rectus femoris and diaphragm-ultrasound imaging), exercise capacity (six-minute walk test and one-minute sit to stand test), balance (brief-balance evaluation systems test) and physical activity (accelerometer). Data will be collected at baseline, at 12 weeks, at 3- and 6-months post-PR.

Changes in the outcome measures will be compared between groups, after multivariate adjustment for possible confounders, and effect sizes will be calculated. A cost-benefit analysis will be conducted.

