### Study design, setting and recruitment

A real-world non-randomised controlled study conducted in the community has been designed. Coordinators of primary healthcare centres will be approached in an arranged meeting to explain the study and those interested to participate will be asked to identify the multidisciplinary team available in their primary healthcare centre. Indication for the minimum staff required will be provided, i.e., a physician, a physiotherapist and a nurse; however, emphasis on the importance to include other professionals (e.g., nutritionist, psychologist, social worker), if available, will be given, following the international recommendations [28, 39, 40]. General practitioners and/or pulmonologists will identify eligible stable patients with a CRD (e.g., COPD, asthma, asthma-COPD overlap, interstitial lung disease, etc.) and their caregivers, and explain the study. Only patients and caregivers with interest in participating will be contacted by the researchers. A meeting will then be arranged to provide written and oral information about the study and collect the informed consent (Additional file 1). The researchers also explained that all data would be kept in databases password protected, using codes and their names would never be disclosed, ensuring the confidentiality and anonymity of all data. Two groups will be composed, experimental (EG) and control (CG). The EG will include patients and caregivers wanting to participate in a 12-week community-based PR programme and the CG will include those age- and disease-matched willing to collaborate in data collection but not in the PR programme. Recruitment started in January 2019, with final data collection expected to be completed in December 2019.

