### Sample size

A sample size estimation with 80% power at 5% significance was calculated to detect significant differences in patients’ health-related quality of life assessed with the SGRQ. The pre-post score achieved in the intervention group of a PR in COPD integrating family-based education and psychosocial support was used (Pre 37.9 ± 18.2 vs. Post 31.4 ± 18.7, *p* < 0.001) [27], resulting in a total sample size of 73 participants. In PR programmes, dropout rates are approximately 20 to 40% [89, 90]. Therefore, 102 participants will be recruited. Sample size calculation was performed using G*Power 3.1.3 (Universität Düsseldorf, Düsseldorf, Germany).

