### Data management and statistical analysis

All variables will be processed in IBM SPSS or MS Excel software. Descriptive statistics, including frequencies, means and standard deviations, medians and interquartile ranges, will be used as appropriate. Short- and medium-term effects of the community-based PR programmes will be verified using paired t-test or Wilcoxon signed-rank tests, accordingly to data normality. Mean scores of continuous variables will be compared between patients and their caregivers using independent samples t-test or Mann Whitney U test, depending on the variable distribution. Pearson correlation coefficient [91] and Bland and Altman plots [92] for continuous variables and Cohen’s k [93] for categorical variables, will be applied to study the relationship and agreement between patients and caregivers. Relationships between variables will be explored with inferential, correlational and univariate/multivariate analyses in SPSS. Differences between the EG and CG at different time points will be assessed using a two-way ANOVA with repeated measures (continuous data), Kruskal-Wallis (ordinal data) and Chi-square or Fisher exact probability tests (nominal data). If missing data is found during the study follow up, the generalized estimating equation’ models will be applied. This method is an extension of generalized linear models to longitudinal data which permits the inclusion of time-dependent variables and the analysis of incomplete data (without imputing missing data), common in longitudinal health studies [94]. A significance level of 0.05 will be used.

Whenever possible, minimal clinically important differences (MCID) will be established, following the current recommendations to integrate both anchor-based and distribution-based approaches [95, 96]. The final MCID for each measure will be pooled using MetaXL 5.3 (EpiGear International, Queensland, Australia), with the input data being the MCID generated by each anchor- and distribution-based method and, when appropriate, the respective confidence interval. A quality effects model [97] will be used and anchor-based methods will weigh more than distribution methods (i.e., 2/3 against 1/3) [98].

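### Controls are matched on age and disease and the Abstract promises confounder adjustment, but the EG-CG analysis as specified contains neither the matching factors nor any adjustment

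*Protocol article*

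**What the plan says.** Under Study design, setting and recruitment the article states: "A real-world non-randomised controlled study conducted in the community has been designed". On how controls are formed it says that "the CG will include those age- and disease-matched willing to collaborate in data collection but not in the PR programme". The Abstract (Methods) describes the same matching at dyad level: "The control group will include dyads age- and disease-matched willing to collaborate in data collection but not in PR". Neither place gives a ratio, a caliper, or whether matching is individual or by frequency.

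The Abstract also commits to adjustment: "Changes in the outcome measures will be compared between groups, after multivariate adjustment for possible confounders, and effect sizes will be calculated". It names no confounders.

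Under Data management and statistical analysis, the EG-CG comparison of continuous outcomes is set as follows: "Differences between the EG and CG at different time points will be assessed using a two-way ANOVA with repeated measures (continuous data". For other outcomes the section gives "Kruskal-Wallis (ordinal data) and Chi-square or Fisher exact probability tests (nominal data". It then adds: "If missing data is found during the study follow up, the generalized estimating equation" approach will be used. None of these sentences mentions age, diagnosis, a matched set or a covariate. The section refers to multivariate analyses only for exploring relationships between variables.

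On losses, the Sample size section says: "In PR programmes, dropout rates are approximately 20 to 40" per cent.

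**The concern.** In a non-randomised study where patients choose their own group, matching on age and disease is the only control of confounding at the design stage that the article states. The analysis should carry it forward, for two reasons.

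- **Balance.** Matching balances the groups at enrolment. With substantial dropout, the patients still observed may no longer be balanced. An analysis with only group and time cannot correct that.
- **Precision.** If the matching factors predict the outcome being compared, leaving them out puts their variation into the error term. The standard error is then too large and the test conservative.

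The EG-CG comparison is the only controlled evidence on health-related quality of life in this study, so both matter. The Abstract promises an adjusted comparison, so the two sections also need reconciling.

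**Working it through.** **1. The plan's own figure.** The sample size uses an SGRQ change from 37.9 (SD 18.2) to 31.4 (SD 18.7), a difference of 6.5, with 80% power at 5%. For a paired t-test the SD of change is sqrt(18.2² + 18.7² - 2·r·18.2·18.7). The pre-post correlation r is not stated. Two-sided, r = 0.40 gives 78, r = 0.44 gives 73 and r = 0.50 gives 66. The stated 73 is therefore reached at r of about 0.44 (SD of change 19.5). Two independent groups compared on the same means and SDs would need 127 per group, so 73 is a one-group pre-post figure. It neither supports nor contradicts a claim about matching. The recruited number is 73 × 1.4 = 102.2, stated as 102.

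**2. What the stated analyses can hold.** A two-way repeated-measures ANOVA for EG versus CG over time has group and time as its factors. Kruskal-Wallis, chi-square and Fisher tests compare independent groups and take no covariates. GEE could take covariates or clustering by matched set, but neither is named.

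**3. Balance after dropout.** Suppose a diagnosis makes up shares p_EG and p_CG of the retained patients, and its mean change differs by D from that of the other patients. The unadjusted EG-CG difference in change is then shifted by (p_EG - p_CG) × D. Matching makes the first factor close to zero at enrolment, and it stays there if dropout by diagnosis is alike in both groups. If it is not, only a model containing diagnosis corrects the shift. The same holds for age. The documents give no group-specific dropout, so the shift cannot be sized. If matching were one-to-one and dropout independent, intact pairs would be 0.8² = 64% at 20% dropout and 0.6² = 36% at 40%.

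**4. Precision.** Let rho be the correlation within matched sets of the quantity analysed or, equivalently under exact matching, the share of its variance that the matching factors explain. Then SE(unmatched)/SE(matched) = 1/sqrt(1-rho), and the true two-sided error of a nominal 5% unmatched test is 2·(1 - Φ(1.96/sqrt(1-rho))). Power below is for a 6.5-point difference in change, with SD of change 18.5 (r = 0.5, assumed). The sizes of 51 and 73 per group are scenarios, since the article gives no CG size.

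| rho (assumed) | SE overstated by | True type I error | Power, 51 per group | Power, 73 per group |
|---|---|---|---|---|
| 0 | 0% | 5.0% | 42.8% | 56.7% |
| 0.05 | 2.6% | 4.4% | 44.6% | 58.8% |
| 0.10 | 5.4% | 3.9% | 46.6% | 61.1% |
| 0.20 | 11.8% | 2.8% | 51.1% | 66.2% |
| 0.30 | 19.5% | 1.9% | 56.6% | 72.0% |

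The power columns show the analysis that uses the matching. The unmatched comparator is the rho = 0 row, which moves by less than 1.5 points over this range: at rho = 0.30 with 51 per group, (1.778 - 1.960)/sqrt(0.7) = -0.22, or about 41%. With SD 19.5 and 73 pairs, a simulation gave 52% unmatched against 60% matched at rho = 0.20, a similar gap.

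**5. Which correlation counts.** For the group-by-time effect only the correlation of changes matters. In a simulation of 51 pairs with SD of change about 14:

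- Level correlation 0.19, change correlation 0: SE of the difference in change 2.76 unmatched against 2.75 matched, with type I error about 5% for both.
- Level correlation 0.19, change correlation 0.18: SE 2.77 against 2.49, with unmatched type I error 3.3%.

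**The case against.** The strongest reply is that the Abstract already promises adjustment for confounders, with age and disease the obvious candidates, and that an article normally leaves the covariate list to a fuller document. Silence in the analysis section would then be condensation, not exclusion. Part of this stands: the article never says that age and diagnosis are excluded, and a missing covariate list alone would be no finding. But the analysis section goes further than silence. It fixes named methods for exactly this comparison, and several of them cannot be adjusted. Followed as written, they do not deliver what the Abstract promises.

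Four further objections stand and limit the point:

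- One-to-one pairs are not stated. Under frequency matching there is no matched set to model.
- The precision loss rests on an assumed rho for change and may be nil. Where it occurs, the test is conservative, so false positives do not rise.
- The article gives one dropout range for rehabilitation programmes and no rates by group, so differential loss is a risk, not a stated expectation.
- EG-CG differences are secondary objective 2.2, worded as exploratory, and the sample size rests on the pre-post comparison.

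GEE keeps patients with incomplete data, which helps. Without age and diagnosis in the model, however, it does not account for losses that depend on them.

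**Conclusion.** The point holds as an inconsistency with a practical consequence. The study matches on age and disease and promises adjustment, but the EG-CG analysis it specifies includes neither the matching factors nor any adjustment. The more important consequence is that age or diagnosis imbalance arising from differential dropout would go uncorrected. The documents do not allow its size to be stated. The second is a possible loss of precision: nil at rho = 0, 3 to 5% in the standard error at rho 0.05 to 0.10, and 12% at 0.20. All values of rho are assumptions.

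A reader might infer that the standard error is definitely too large and that the benefit of matching is lost. The documents do not support either. The first requires that age and diagnosis predict change, on which the article gives no information. The second overlooks that matching still balances the retained patients, so far as losses are similar, without any model term. Nor do the documents support treating the data as matched pairs. The change is worth making because it is cheap, but it concerns a secondary, exploratory comparison.

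**What to change.** Reconcile Data management and statistical analysis with the Abstract:

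- **Continuous outcomes.** State that the EG-CG model (repeated-measures ANOVA or mixed model, or GEE) includes age as a continuous covariate and diagnosis group, each with its interaction with visit. The interactions are needed because a main effect alone shifts all visits equally and does not act on the group-by-visit contrast. Name the other confounders that the Abstract has in mind.
- **Ordinal and nominal outcomes.** Replace the unadjusted independent-group tests with covariate-adjusted models, for example ordinal and logistic regression.
- **Matching.** State whether it is individual or by frequency. Only if it is individual, add the matched set as a cluster or random effect, and keep members whose partner has dropped out.

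The cost is wording and a few degrees of freedom; small diagnosis groups should be combined. No new data are needed, since age is already collected and diagnosis is required for eligibility and matching.

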Another anticipated limitation is the recruitment of caregivers. Caregivers are rarely included in PR programmes therefore, they might not be aware of the possible response that PR can provide not only to patients but for the whole family. The importance of their inclusion will be discussed with patients and caregivers when explaining the study. A written information sheet highlighting the importance of their inclusion will be provided to promote their inclusion.

Moreover, acknowledging the benefits that PR has for patients with CRD, not offering PR to all eligible patients will never be considered. Therefore, the CG will be composed of only those patients who are willing to participate in data collection but do not want take part in the PR programme. This might lead to difficulties in recruiting for the CG. Nevertheless, with the permission of patients and caregivers, a telephone call will be made prior to data collection to minimise dropouts.

A follow-up period of 6 months could be too short to draw conclusions about the medium- or long-term changes in patients’ health and non-health measures, necessary for cost-benefit analysis. However, limited funding is available for the study.

Finally, obtaining cooperation of patients during the ultrasound measurements of the diaphragm might be challenging as these patients often present significant dyspnoea and fatigue levels, limiting their collaboration in the requested breathing manoeuvres.

We expect that this study will enhance the patients’ access to PR and provide an evidence-based insight into the economic benefit of community-based PR in chronic respiratory diseases, through a cost-benefit analysis.

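### The abstract promises a confounder-adjusted comparison of EG with CG, but the analysis section assigns it to tests with no covariates, in a study whose controls chose not to have PR

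*Protocol article*

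**What the plan says.** The design is described as "A real-world non-randomised controlled study conducted in the community has been designed" (Study design, setting and recruitment). Groups form by participants' own choice: "the CG will include those age- and disease-matched willing to collaborate in data collection but not in the PR programme". The Discussion repeats that "the CG will be composed of only those patients who are willing to participate in data collection but do not want take part in the" programme.

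The abstract's Methods paragraph states: "Changes in the outcome measures will be compared between groups, after multivariate adjustment for possible confounders, and effect sizes will be calculated".

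The section Data management and statistical analysis gives the EG-CG comparison its own sentence: "Differences between the EG and CG at different time points will be assessed using a two-way ANOVA with repeated measures" for continuous data, then "Kruskal-Wallis (ordinal data) and Chi-square or Fisher exact probability tests (nominal data". It lists no covariate, confounder, ANCOVA or propensity method. Multivariate analysis is mentioned once, for another purpose: "Relationships between variables will be explored with inferential, correlational and univariate/multivariate analyses in SPSS". GEE models are to be used if follow-up data are missing. The reasons given are incomplete data and time-dependent variables, not confounding.

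**The concern.** Willingness to undergo PR decides who is in which group. People who decline may differ from those who accept in severity, comorbidity, oxygen use, exercise capacity or work status. Each of these may also affect later SGRQ, exacerbations and costs. Matching on age and diagnosis leaves them free to differ, and the Background says that all grades of disease will be enrolled.

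The other named analysis of effect is a paired pre-post test, which cannot separate PR from time trend or regression to the mean. The EG-CG contrast is therefore the only controlled evidence of effect. It also reaches the economic objective, because an incremental cost per exacerbation or healthcare use avoided needs a comparator and the CG is the only one in the study.

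If the abstract and the analysis section both stand, either an adjusted or an unadjusted result could later be presented as the planned one.

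**Working it through.** **1. The statements side by side**

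| Place | Contrast | Adjustment |
|---|---|---|
| Abstract, Methods | Changes, EG vs CG | Multivariate, for possible confounders |
| Analysis section, continuous | EG vs CG over time, two-way repeated-measures ANOVA | None named |
| Analysis section, ordinal and nominal | EG vs CG, Kruskal-Wallis; chi-square or Fisher | None named; these tests take no covariates |
| Analysis section, multivariate sentence | Relationships between variables | Not tied to EG vs CG |
| Analysis section, GEE | Longitudinal data with missing values | Could carry covariates; none named |

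For ordinal and nominal outcomes the abstract's promise cannot be met with the named tests. For continuous outcomes it could be met only by adding something the section does not mention.

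**2. What each named test removes**

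Suppose PR has no effect and EG differs from CG by a constant amount d at every visit.

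- Group by time: (difference at 12 weeks) − (difference at baseline) = d − d = 0. A stable baseline difference is removed.
- A Kruskal-Wallis or chi-square test at 12 weeks compares groups that still differ by d. Baseline is not used.

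Now suppose a characteristic X differs between groups by D on average, and each unit of X alters the change in outcome by g. The group by time contrast is then shifted by g × D. Neither ANOVA nor the single-visit tests remove this.

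**3. How likely the GEE fallback is**

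The Sample size section cites dropout of 20 to 40% and plans to recruit 102. That gives 102 × 0.20 = 20.4 to 102 × 0.40 = 40.8, or roughly 20 to 41 people with missing follow-up. GEE will probably be used, but still with no stated confounders.

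**4. An illustration of size**

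The plan gives no figure for the EG-CG contrast. Its sample size of 73 is a one-group pre-post calculation: difference 37.9 − 31.4 = 6.5, SDs 18.2 and 18.7. A two-sided paired t-test at 80% power gives 73 if the pre-post correlation r is about 0.44, but 66 at r = 0.5 and 40 at r = 0.7. The documents do not state r, so I vary it.

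- SD of change = √(18.2² + 18.7² − 2 × r × 18.2 × 18.7) = 19.53 (r = 0.44), 18.46 (r = 0.5), 14.30 (r = 0.7).
- SE of the difference in change = SD × √(2/n), with n per group.
- Rejection rate with no PR effect and a confounding shift b = 1 − Φ(1.96 − b/SE) + Φ(−1.96 − b/SE).

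I take n = 36 (73 split in two) and n = 73 (the abstract places 73 in the EG; an equal CG is assumed).

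| Assumed shift b (SGRQ points) | n = 36, r = 0.44 / 0.5 / 0.7 | n = 73, r = 0.44 / 0.5 / 0.7 |
|---|---|---|
| 1 | 5.5% / 5.6% / 6.0% | 6.1% / 6.2% / 7.1% |
| 2 | 7.2% / 7.5% / 9.1% | 9.5% / 10.0% / 13.5% |
| 4 | 14.0% / 15.1% / 22.1% | 23.6% / 25.8% / 39.4% |

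Nothing in the documents says which row applies. The table shows only how the error rate responds to a given shift.

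**The case against.** The section never says that the comparison is unadjusted, the abstract states the intention to adjust, and covariate lists are commonly left to an analysis plan that is not shown. This stands as far as the list is concerned. It does not cover the choice of test: the section settles on named tests for this contrast, and three of them cannot carry the promised adjustment.

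GEE accepts covariates and will probably be triggered. That narrows the gap. But adjustment would then hinge on whether someone drops out, and no confounders are named for it.

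The EG-CG clinical comparison falls under objective 2.2, worded as exploratory, while effects are to be verified by paired tests. This is fair and lowers the severity, although the economic objective, which is primary, still needs the comparator.

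Three stronger readings are tempting, and the documents do not support them:

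- A reader might infer that the whole plan ignores baseline. The group by time term does use it; only the ordinal and nominal tests at a single visit do not.
- A reader might turn an assumed baseline SGRQ gap into a bias expressed as a share of the 6.5-point planning difference. That compares a change-score estimate with a baseline-adjusted one, and neither is right by default in self-selected groups. The 6.5 points are also a one-group pre-post change, not an EG-CG effect.
- A reader might infer that every covariate needed is already collected. Data collection lists age, sex, BMI, Charlson index, oxygen and ventilation use, spirometry, mMRC and 6MWT, but no count of exacerbations or healthcare use before enrolment.

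**Conclusion.** The inconsistency is real and should be fixed. The abstract commits to an adjusted EG-CG comparison; the analysis section names methods that do not deliver it and, for ordinal and nominal outcomes, cannot. With a control group of people who did not want PR, matched on two characteristics, the comparison is open to confounding by severity and comorbidity that the trial measures at baseline.

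That the named ANOVA is unadjusted is inferred from the absence of any covariate. The direction and size of the bias cannot be derived from the documents. Under the assumptions above, a shift of 1 point barely moves the 5% error rate (5.5% to 7.1%), while a shift of 4 points raises it to between 14% and 39%. The conclusion does not depend on these figures.

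**What to change.** In Data management and statistical analysis, replace the EG-CG sentence with one covariate-adjusted longitudinal regression per outcome. This can be the GEE already named or a mixed model, used whether or not data are missing. Specify:

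- group, time and group by time, with the baseline value of the outcome;
- a short prespecified covariate set from Data collection, for example age, sex, diagnosis, lung function and Charlson index;
- an ordinal or logistic link for ordinal or nominal outcomes;
- a separate short set suited to caregivers for the WHOQOL-Bref;
- the ANOVA, Kruskal-Wallis and chi-square or Fisher results as descriptive only.

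Propensity weighting is optional. A long covariate list would strain a study of 73 to 102 participants. If exacerbations or healthcare use are to be adjusted for their earlier level, first confirm that a pre-enrolment count is collected.

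The cost is a change of wording and a few degrees of freedom. Adjustment will not remove confounding by motivation, and the Discussion should state this as a limitation.

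### Switching from ANOVA to GEE when data are missing makes GEE the near-certain group comparison, and without weights it can bias the follow-up contrasts if dropout depends on earlier scores differently in the two groups

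*Protocol article*

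**What the plan says.** Under Data management and statistical analysis, EG and CG are to be compared over time by two-way repeated-measures ANOVA for continuous outcomes. The next sentence makes the method depend on completeness: "If missing data is found during the study follow up, the generalized estimating equation" models are then to be used. The reason given is that GEE "permits the inclusion of time-dependent variables and the analysis of incomplete data (without imputing missing data"). The article names no weighting, working correlation or missingness assumption.

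Under Sample size, the article says that in pulmonary rehabilitation (PR) programmes "dropout rates are approximately 20 to 40"%, and continues: "Therefore, 102 participants will be recruited". Under Data collection there are four visits: baseline, week 12, and 3 and 6 months after the programme. Under Study design and in the Discussion, EG consists of people who want the programme and CG of people who agree to be measured but do not want it.

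**The concern.** The article's own dropout figure makes complete data implausible. ANOVA is therefore the named method but will almost surely not be the one used, and GEE is in effect the plan.

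The reason given for GEE is that it needs no imputation. That makes it feasible with incomplete records but does not make it unbiased. Suppose people with worse SGRQ scores leave EG more often, while CG loses people for unrelated reasons. Those still seen in EG at 3 and 6 months are then a favourable selection, and a method that compares observed means takes part of that selection for effect. If those who feel well leave instead, the error runs the other way. A different dropout mechanism in each group is plausible here, because the groups are self-selected and only one attends a 12-week programme. At stake are the 3- and 6-month group contrasts.

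**Working it through.** **1. Will the switch be triggered?** Inputs from Sample size: 73 evaluable, 102 recruited, dropout 20 to 40%.

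- The recruitment figure is reproduced by 73 × 1.40 = 102.2, so 102.
- Expected completers: 102 × 0.80 = 81.6 and 102 × 0.60 = 61.2. About 20 to 41 people would have incomplete data.
- Chance that nobody is missing at 20% independent dropout: 0.8^102 = exp(102 × ln 0.8) = exp(-22.8), about 1 in 10^10.
- The cited rate is for PR programmes and not for controls. If only EG lost people and EG were half of the sample (an assumption; no ratio is given), the chance is 0.8^51 = exp(-11.4), about 1 in 90,000.

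The GEE branch is close to certain.

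**2. What GEE needs.** GEE solves Σ D′V⁻¹(y − μ) = 0 over the observed records. With an independence V and a group × visit mean, the month-6 contrast is the difference between the means of those still observed. That is unbiased only if being observed is unrelated to the outcome given the covariates in μ. With a linear mean and a correctly specified V, the equations match the Gaussian likelihood equations, and missing at random is then essentially enough.

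**3. How large could it be?** From the document: effect 31.4 − 37.9 = -6.5 and SD (18.2 + 18.7)/2 = 18.45. The effect is a one-group pre-post change, used here as the true EG–CG contrast. Correlation 0.5, the dropout mechanism and the absence of covariates are assumptions. Month-6 estimates, 20,000 simulated participants, Monte Carlo standard error about 0.3, at 20% / 40% dropout:

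| Dropout mechanism | GEE, independence | GEE, exchangeable (correct here) |
|---|---|---|
| Completely at random | -6.08 / -6.91 | -6.08 / -6.87 |
| Depends on last score, alike in both groups | -6.51 / -6.62 | -6.50 / -6.60 |
| Depends on last score, EG only | -8.22 / -9.91 | -6.55 / -6.38 |
| Opposite directions in the two groups (extreme) | -10.10 / -13.50 | -6.79 / -6.68 |

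For EG-only dependence, the independence bias is -8.22 + 6.5 = -1.7 and -9.91 + 6.5 = -3.4. A completers-only comparison of change from baseline, which is what ANOVA on complete cases amounts to, gave -5.95 / -5.11 in that row. Staying with ANOVA is therefore no remedy.

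**4. Sensitivity to the assumptions.** These runs place EG-only dropout after week 12, with odds × 2.7 per SD worse SGRQ and 20 to 40% dropout.

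- Constant correlation, independence GEE: -7.8 to -9.2 (r = 0.44) and -8.8 to -10.8 (r = 0.7).
- Correlation decaying over time, independence GEE: -7.2 to -9.6.
- Correlation decaying over time, exchangeable GEE: -5.5 to -6.2, an error of 0.3 to 1.0 towards zero. A separate run with decaying correlation (r = 0.7, 40% dropout from baseline on) gave -6.38 at month 6, within noise of the truth.
- Independence GEE adjusted for baseline SGRQ: -7.2 to -8.1. If dropout depends on baseline only: -6.5 to -6.6.

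Across the unadjusted independence runs with EG-only dependence, the bias is 7.2 − 6.5 = 0.7 to 10.8 − 6.5 = 4.3 points, or about 1 to 4.

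**The case against.** The strongest reply is that the figures measure a poor working correlation and not GEE as such. The article never says independence, and the choice of working correlation is something an article may leave to the analysis plan. This stands: a correct exchangeable structure removes nearly all the bias, and its absence from the article is not the point. Exchangeable is not a guarantee either, because correlation that decays with time can leave an error, though a modest one.

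Second, the abstract promises adjustment for confounders. If baseline SGRQ is among them, which the article does not say, the bias is roughly 1 to 1.5 points. This also stands.

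Third, the dropout mechanism is assumed. The cited rate covers programme dropout, whereas the step 4 runs place losses after the programme has ended, and the article plans telephone calls to limit losses. This is fair, and it is why no size can be claimed.

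Fourth, the switch is a rule stated in advance and triggered by missingness, not by results. That is right; the objection is to the method it leads to.

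Fifth, the article tests short- and medium-term effects, the wording of primary objective 1.1, by paired tests. The EG–CG comparison answers secondary objective 2.2 most directly. A reader might infer that the primary analysis is undermined, but the text does not clearly support that.

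A reader might also infer that the cost ratios are overstated. The documents do not support this: neither SGRQ nor GEE is named as an input to them, and with a positive incremental cost an overstated benefit would lower the cost per unit gained.

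**Conclusion.** The point holds as a conditional one. The article fixes GEE as its answer to incomplete data, its own dropout figure makes that answer near certain to be used, and the reason given does not establish validity. If dropout depends on earlier SGRQ scores differently in EG and CG, and those scores are not in the model, the 3- and 6-month group contrasts can be biased.

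The figure of about 1 to 4 points assumes EG-only score dependence, an independence working correlation and no covariates. The size and direction cannot be derived from the documents, so a reading that the medium-term benefit will be overstated by several points goes too far. Nor is a mixed model always better than GEE: with a correct working correlation the two rest on much the same assumption. The case for change is that a likelihood model with unstructured covariance relies on missing at random without a guess at the correlation. That model was not itself simulated; this rests on the known property of likelihood methods.

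**What to change.** Replace the ANOVA/GEE switch by one pre-specified analysis for continuous outcomes, used whatever the amount of missing data. Use a linear mixed model for repeated measures, fitted by REML with unstructured covariance. Include group, visit, group × visit, baseline SGRQ (or the baseline value of the outcome analysed) and the planned confounders, and state missing at random as the assumption. If GEE is preferred, weight it by the inverse probability of remaining under observation. A missing-not-at-random sensitivity analysis would be useful but is optional.

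The cost is analysis wording and slightly more modelling work. No data or visits are added, and mixed models are available in the SPSS package already named. With baseline as a covariate, three follow-up visits need 3 × 4 / 2 = 6 covariance parameters. At about 102 participants this may still fail to converge, so a simpler fallback structure should be named in advance.
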